# **Project summary (~250 words)**

Diabetes mellitus is one of the major intractable public health problems in developing countries including Nepal. The dietary approach is of paramount significance in the management of type 2 diabetes. There is still a lack of evidence on a dietitian-led dietary approach to the management of T2DM patients in the Nepalese context. The aims of this study is to examine the effectiveness of dietitian-led dietary approach to management of diabetes on reduction of HbA1c level, nutrition education score and macronutrient intake among T2DM patients in a tertiary care hospital in Kathmandu, Nepal.

The Dietary Approach to the Management of Diabetes (DIAM-D) trial is a hospital-based, open-label, two-armed, randomized control trial. A total of 156 participants with T2DM having HbA1c >6.5% will be enrolled in the study. Participants will be consecutively enrolled and assigned to receive nutrition education and counseling (NEC) and diet plan in the intervention group (n=78) and usual routine care in the control group (n=78) randomly. The NEC will be provided to participants on group session and the diet plan will be face-to-face individual basis at the time of enrollment and follow-ups will be done every month. Baseline data will be collected using a structured questionnaire for an interview and the biochemical tests will be measured. Baseline data will be collected at the time of enrollment, midline in three months and end-line data collection in 6 months. The primary outcome of the study will be a difference in mean change (from baseline, midline to 6 months) in the HbA1c level between the two study arms from baseline to end line. The secondary outcomes measure will be changed in biochemical and clinical parameters between the two arms at baseline midline to six months. Data will be entered using Epidata Software and transferred to the STATA/MP version 14.1 for further analysis. Data will be analyzed using an intention-to-treat basis. Independent sampele t-test will be used to estimates changes between the intervention and usual care arms.

**Key word:** Dietitian, Dietary approach, Management, Diabetes, Nepal

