## **7.10. Tools and techniques for data collection**

The baseline and end-line data collection will be performed in both intervention and usual care arm. A pre-tetsed culturally accepted and adapted, Nepali translated version tools and techniques will be used to conduct the study. A total of three data collection team who have graduated in health or nutrition science will be hired from the local area.

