**Tools and procedure**

- Screening checklist: This checklist entails information regarding inclusion and exclusion criteria.
- Baseline questionnaire: The study participants’ information on Socio-demographic, such as age, sex, occupation, educational level, residence, religion, ethnicity, etc. will be taken by using a face-to-face structured questionnaire interview. The questionnaire will be adopted from NDHS 2017 and STEP Survey 2019^22,23^.
- Dietary intake: Dietary intake assessment will be assessed before intervention (baseline) and after intervention (end line) using 24-hour qualitative dietary recall and food frequency questionnaire (FFQ) to compute the macronutrient intake level.
- Biochemical measurements: A fasting blood sample for HbA1c, fasting glucose, liver function test (bilirubin, ALT, AST ALP, and albumin) and lipid profile (total cholesterol, triglycerides, HDL, LDL) will be measured at baselines, three months and six months. All blood samples will be taken and handled, analyzed and disposed of according to local practice policy.
- Quality of life: The Problem Areas in Diabetes (PAID) score^24^, a 20 items questionnaire measuring the problems related to emotions, treatment, food and social support, will be measured at baselines and 12 months.
- Physical measurement: Height will be measured using a stadiometer to the nearest 1cm. Participants' weight will be measured to the nearest 0.1kg using the Seca weighing scale. BMI will be measured calculated using the widely used formula (BMI= weight (kg)/height (m)^2^), and waist Hip Circumference (WHR) will be measured using measuring tape. Systolic and diastolic blood pressure will be measured three times after 5 minute seated rest using a sphygmomanometer and stethoscope. The trained data enumerator will be taking physical measurements according to the study manual procedures.
- Nutritional knowledge score on diabetes: The diabetes knowledge test (DKT)^25^will be used to assess the nutritional knowledge score on diabetes.
- Physical activity: The physical activity will be measured using the Global Physical activity questionnaire recommended by WHO STEPwise surveillance tools^23^.
- Monitoring checklist: This will be used as every month follow up checklist. The information on lifestyle modification such as consumption of food, physical activities, adherence, and diabetic-related minor and major complication will be sought.

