## **7.11. Management protocol of patients/participants if applicable**

In the intervention phase, the educational and diet plan package will be developed. All the intervention packages will be approved by a multi-disciplinary expert team comprising an endocrinologist and dietitian prior to the intervention. Patients in the usual care arm will receive routine care as to how he/she is practicing in their daily life. Routine care includes general knowledge on diabetes disease process, blood glucose monitoring, a healthy lifestyle, preventing treating diabetes complications and developing personalized strategies for the decision-making process ^26^. The intervention package will include mainly two-phase, nutritional counseling emphasis on lifestyle modification of diabetes patients and individual basis diet plan for each T2DM patients for intervention arm. The nutrition education and counseling and individual diet plan will be applied by trained dietitians.

In the first phase, participants in the intervention arm will receive a nutrition counseling session. Nutrition counseling package consists of six modules (knowledge about diabetes and additional information, treatment of diabetes, food-based dietary guidelines, and exercise guidance, knowledge of hypoglycemia treatment, foot care, medication, and blood glucose monitoring)^12,16^ which will be developed as a training manual and approved by multi-disciplinary expert team. Nutritional counseling will be provided by a dietitian who had to work at the participating working center. Every month, follow-up will be done to reemphasize the key message.

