| 3 | Food-based dietary guidelines, healthy eating pattern | Dietary guidelines for each food group such as starch, fruits and vegetables and additional information on diabetes.  A nutrition education brochure will be provided. Information will be emphasis on healthy eating habits such as information about glycemic index and glycemic load of food, the difference between simple and complex carbohydrate, difference between saturated  and unsaturated fat, total calorie intake according to their needs, and calorie contains in beverage and alcohol  Overview of food groups and their roles in the body. |
| 4 | Diet planning: serving size and meal frequency | Guidelines of serving size and meal frequency and its importance  Demonstration: serving size (household measurement) |
| 5 | Knowledge of hypoglycemia treatment  and foot care | Guidelines of knowledge of hypoglycemia and its treatment knowledge of foot care practices |

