# **Safety considerations**

Safety of research participants will be ensured by well maintaining confidentiality of the personal information given by the participants.

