# **Ethical issues and considerations regarding human participants**

The study will be conducted as per the guidelines formulated in the Declaration of Helsinki and ethical approval from the Nepal Health Research Council before commencing the research. This study will be registered with ClinicalTrials.gov. Every document used including questionnaire, consent, and information sheet will be submitted to the Board along with the methodology, study design, and evidence. After feedback, correction and modifications will be made into a questionnaire, and consent.

We will constitute a Data Safety Management Board (DSMB) comprising of an Endocrinologist/Physician, a dietitian, and one statistician. The DSMB members will prepare a study stopping rules and will review all the possible effects reported in the study on a quarterly basis. They will examine all participants' health status like comorbidities and decide if the study should be continued or terminated. After completed a follow up of 1/3rd of the study participants, DSMB will review data and recommend continuation, modification or termination. Any important protocol modifications, such as change of eligibility criteria, outcome analysis will be thoroughly communicated with members and will obtain amendments from NHRC.

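### Complications are asked about only on a monthly checklist with no arm named; monthly follow-up is described only for the intervention, so harm ascertainment may differ by arm

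*Protocol*

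**What the plan says.** Section 7.10 (Tools and procedure) lists the study instruments. The last is the monthly one: "Monitoring checklist: This will be used as every month follow up checklist". Besides diet and physical activity, it covers harm: "adherence, and diabetic-related minor and major complication will be sought". No arm is named for it.

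The same section opens by fixing what both arms share: "The baseline and end-line data collection will be performed in both intervention and usual care arm". Blood tests are added at three months, again with no arm named.

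Monthly contact is mentioned elsewhere only with the intervention. The Project summary attaches it to the education sessions and diet plan: "at the time of enrollment and follow-ups will be done every month". In 7.11, under the first phase of the intervention package: "Every month, follow-up will be done to reemphasize the key message". The second phase, the individual diet plan, repeats the monthly schedule. The usual-care arm is described as continuing routine care.

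Under Ethical issues, the DSMB reviews possible effects quarterly and again after one third of participants have been followed. It examines the health status of all participants, comorbidities included, and is to "decide if the study should be continued or terminated". No data source is named. The Safety considerations section consists of one sentence: "Safety of research participants will be ensured by well maintaining confidentiality of the personal information given by the participants".

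**The concern.** Open-ended harms such as hypoglycaemic episodes, complications and new diagnoses are mostly recorded when somebody asks. If one arm is asked monthly and the other on no stated occasion, the recorded rates differ even when the true rates are equal. The diet arm could then look harmful because it is questioned more often, or a true excess could be put down to closer questioning.

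The trial is open-label and its DSMB may end it, so the question of who is asked, with which form and when, matters during the trial as well as at reporting. It also cannot be repaired at analysis, because an event nobody asked about leaves no record. This makes it a matter for the data-collection section of the protocol and not one to leave to an analysis plan.

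**Working it through.** The protocol states no figure on this point, so there is nothing to reproduce. The check is a reading of the sections side by side, followed by an illustration on assumed values.

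**Step 1. Where could a clinical event be recorded?**

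| Source | Arm | Records complications, hypoglycaemia or new comorbidity? |
|---|---|---|
| Monthly monitoring checklist (7.10) | Not named | Yes, complications |
| Monthly follow-up (Project summary; 7.11, both phases) | Intervention | Checklist not mentioned there |
| Usual-care description (7.11) | Usual care | No study contact described |
| Screening checklist (7.10; comorbidity criterion in 7.7) | Both, before randomization | Comorbidity at entry only |
| Main questionnaire, baseline/end line | Both | No |
| Blood tests at 0, 3 and 6 months; blood pressure; current medication | Not restricted | No; measurements and drug list only |

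**Step 2. Does any item on the shared questionnaire come close?** Items 9 and 19 of the PAID section mention low blood sugar reactions and complications, but each is a 0 to 4 rating of distress and not an event record. The diabetes knowledge section tests what the patient knows. No item asks about hospital contact or a new diagnosis.

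**Step 3. Reading.** The one tool that asks about complications is monthly, and every monthly contact whose recipients are identified belongs to the intervention. No sentence schedules a complication enquiry in usual care, and none rules it out.

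**Step 4. What unequal capture could do (illustration only).** The protocol gives no complication rate and no capture rate, so both are assumed.

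- Review size: 156 / 3 = 52 participants, about 26 per arm if the arms are equally represented. Full size: 78 per arm.
- Let p be the true risk, equal in both arms, with full capture in the intervention arm and a captured fraction c in usual care.
- P(spurious excess) = sum over i > j with two-sided Fisher p < 0.05 of Bin(i; n, p) × Bin(j; n, p × c).

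| n per arm | p | c = 0 | c = 0.5 | c = 1 |
|---|---|---|---|---|
| 26 | 10% | 4.0% | 1.5% | 0.5% |
| 26 | 20% | 42.3% | 9.2% | 1.1% |
| 26 | 30% | 83.7% | 15.9% | 1.2% |
| 78 | 10% | 80.4% | 13.7% | 1.4% |
| 78 | 20% | 99.9% | 33.8% | 1.6% |
| 78 | 30% | >99.9% | 55.1% | 1.7% |

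For example, at n = 26, p = 20% and c = 0.5, the expected recorded events are 26 × 0.20 = 5.2 against 26 × 0.20 × 0.5 = 2.6.

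A second view uses rate ratios with equal true rates. If monthly questioning captures an assumed 90% and later recall in controls an assumed 40%, 60% or 80%, the apparent ratio is 0.90/0.40 = 2.25, 0.90/0.60 = 1.50 or 0.90/0.80 = 1.13.

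**The case against.** The strongest reply is that one-sidedness is inferred from silence. The checklist stands in a general list of tools, beside blood tests that also carry no arm label, and it would be inconsistent to treat one as shared and the other as intervention-only. The checklist is not reproduced, the study-design figure is not shown, and a data-collection manual is still to be written. The attached questionnaire is also not the complete data set: the food frequency questionnaire and liver tests named in 7.10 do not appear on it. All of this stands, and it is why the point says that ascertainment may differ.

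Several stronger readings are tempting and not supported:

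- A reader might infer that the DSMB would judge harm on one-sided data, or could not reach its decision. The text intends review of all participants, and laboratory values, blood pressure and medication are not limited to one arm.
- A reader might count 78 × 6 = 468 complication enquiries against 0. That turns silence into zero and assumes six fully attended contacts. The work plan marks three months of intervention, and the budget pays the dietitian for three.
- A reader might take Table 1 to name hypoglycaemia as a risk of the diet. "Guidelines of knowledge of hypoglycemia and its treatment" is a teaching topic in a module, and patients on insulin are excluded.
- The documents plan no between-arm test of complications, so the spurious findings in the illustration would arise only if somebody made that comparison. A board that may stop the trial has reason to make it informally.

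It can also be said that one clause naming the arm would settle the matter. It would settle the ambiguity only. If the answer is intervention only, usual care still has no event record. If the answer is both arms, controls would be questioned monthly about food, activity and adherence, a contact that 7.11 does not describe, in a trial whose Limitations section already worries about contamination between arms.

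**Conclusion.** The point holds as a gap in how harms are collected. On the most natural reading of 7.10 and 7.11, complications are asked about in the intervention arm and no enquiry is scheduled in usual care. The other reading remains open, because the protocol is silent and does not exclude usual care. The gap is confined to clinical events: complications, hypoglycaemic episodes and new comorbidities.

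Its numerical size is unknown. The illustration shows that the consequence runs from negligible, with rare events or near-equal capture, to large, with common events and little or no capture in controls. These results rest entirely on assumed risks and capture fractions and should not be quoted as properties of this trial. The case for a change rests on the text: the DSMB is given a decision about all participants, and no event record is stated for one of the two arms.

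**What to change.** 1. In 7.10, add a few identical event items to the form used in both arms at the 3- and 6-month assessments, with the same recall window: hypoglycaemic episodes, hospital or emergency contact, and new diagnosis or complication. The attached form is headed for baseline and end line, so these items also need a place at midline.
2. In 7.10, state which arm or arms use the monthly checklist. If only the intervention arm does, keep it for care and adherence.
3. Under Ethical issues, state which data the DSMB receives, and that any between-arm comparison of harm given to it or published uses the shared items.

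The cost is a few questions at assessments already planned, and a short amendment, with no added visit or staff. The drawback is that recall over about three months is coarser than monthly questioning, so some minor events will be missed in both arms.

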## **7.11. Management protocol of patients/participants if applicable**

In the intervention phase, the educational and diet plan package will be developed. All the intervention packages will be approved by a multi-disciplinary expert team comprising an endocrinologist and dietitian prior to the intervention. Patients in the usual care arm will receive routine care as to how he/she is practicing in their daily life. Routine care includes general knowledge on diabetes disease process, blood glucose monitoring, a healthy lifestyle, preventing treating diabetes complications and developing personalized strategies for the decision-making process ^26^. The intervention package will include mainly two-phase, nutritional counseling emphasis on lifestyle modification of diabetes patients and individual basis diet plan for each T2DM patients for intervention arm. The nutrition education and counseling and individual diet plan will be applied by trained dietitians.

In the first phase, participants in the intervention arm will receive a nutrition counseling session. Nutrition counseling package consists of six modules (knowledge about diabetes and additional information, treatment of diabetes, food-based dietary guidelines, and exercise guidance, knowledge of hypoglycemia treatment, foot care, medication, and blood glucose monitoring)^12,16^ which will be developed as a training manual and approved by multi-disciplinary expert team. Nutritional counseling will be provided by a dietitian who had to work at the participating working center. Every month, follow-up will be done to reemphasize the key message.

In the second phase, all patients in the intervention arm will be provided an individualized diet plan to reinforce the concept of controlling the serving size of foods every month which will be lasted for 45-60 minutes. During the patient's visits to OPD, the dietitian will obtain daily nutrient intake by asking the patients to recall the foods and beverages consumed for the past 24 hours. Each participant will be given an individual basis diet plan within the limit of the acceptable macronutrient distribution range (AMDR) ^20^. Energy requirements will be prescribed by a dietitian for each participant based on the patient's height, weight, and physical activity level according to the guidelines of the American diabetic association (ADA)^26^. Energy distribution will be set in accordance with the limit of AMDR i.e. protein 10-35%, fat 20-35%, and carbohydrate 45-65%)^20^. This guideline will be developed for the Nepalese population based on the ADMR compositions includes the use of a food exchange portion in diabetic diet planning. One piece of food exchange portion is defined as one serving for every 80 kcal of a food product. Thus, a similar type of food exchange portion can be exchanged where the nutritional value is almost the same. The individual total energy required per day is calculated according to the individual weight and daily physical activity level using Harris-Benedict equations. Balanced diet for each patient will be planned and the total day's diet plan is distributed into five meal patterns such as breakfast, launch, snack, and dinner and a bedtime snack. In order to avoid excessive energy intake and assure a balanced diet, we emphasize moderate carbohydrates, moderate fat foods and consuming foods rich in fiber and micronutrients. Follow up will be done every month. All educational materials will be developed in English and then translated into Nepalese language.

Table 1 Content of Nutrition Education and Counseling Module for DIAM-D trial

| SN | Topic | Module |
| --- | --- | --- |
| 1 | Knowledge about diabetes mellitus | Basic concept of nature of diabetes, causes and risk factors, types, clinical features, insulin action, body response to food in diabetes and non-diabetes state and complication |
| 2 | Treatment of diabetes | Diet alone, diet and drugs or diet and insulin, exercise and their  role in treatment of diabetes |
| 3 | Food-based dietary guidelines, healthy eating pattern | Dietary guidelines for each food group such as starch, fruits and vegetables and additional information on diabetes.  A nutrition education brochure will be provided. Information will be emphasis on healthy eating habits such as information about glycemic index and glycemic load of food, the difference between simple and complex carbohydrate, difference between saturated  and unsaturated fat, total calorie intake according to their needs, and calorie contains in beverage and alcohol  Overview of food groups and their roles in the body. |
| 4 | Diet planning: serving size and meal frequency | Guidelines of serving size and meal frequency and its importance  Demonstration: serving size (household measurement) |
| 5 | Knowledge of hypoglycemia treatment  and foot care | Guidelines of knowledge of hypoglycemia and its treatment knowledge of foot care practices |

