## **7.9. Expected time and duration of the study**

The study will be carried out for six months, from baseline data collection, follow-up midline data collection and end-line data collection for outcome measure.

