# **Work plan**

| **Gantt chart** | | | | | | | | | | | | | | | |
| --- | --- | --- | --- | --- | --- | --- | --- | --- | --- | --- | --- | --- | --- | --- | --- |
| S.N | Activities | **2019 A.D** | | **2020 A.D.** | | | **2021 AD** | | | | | | | | |
|  |  | **Nov** | **Dec** |  | | | **Jan** | **Feb** | **March** | **April** | **May** | **June** | **July** | **Sept** | **Oct** |
| 1 | Drafting proposal | **×** |  |  |  |  |  |  |  |  |  |  |  |  |  |
| 2 | Proposal submitted to UGC and under review |  | **×** | **×** | **×** |  |  |  |  |  |  |  |  |  |  |
| 3 | Submission and approve proposal to NHRC |  |  |  | **×** | **×** |  |  |  |  |  |  |  |  |  |
| 4 | Tools development |  |  |  |  | **×** |  |  |  |  |  |  |  |  |  |
| 5 | Nutrition counselling and diet plan guidelines developed. |  |  |  |  |  | **×** |  |  |  |  |  |  |  |  |
| 6 | Orientation to stakeholders  And guidelines approval |  |  |  |  |  | **×** |  |  |  |  |  |  |  |  |
| 7 | Training of thesis writing students |  |  |  |  |  | **×** |  |  |  |  |  |  |  |  |
| 8 | Sampling framework |  |  |  |  |  |  | **×** |  |  |  |  |  |  |  |
| 9 | Finalization of intervention and usual care arms in target hospital |  |  |  |  |  |  | **×** |  |  |  |  |  |  |  |
| 10 | Tools pre-testing and finalization |  |  |  |  |  |  | **×** |  |  |  |  |  |  |  |
| 11 | Finalization of research participants |  |  |  |  |  |  |  | **×** |  |  |  |  |  |  |
|  | Baseline data collection |  |  |  |  |  |  |  |  | **×** |  |  |  |  |  |
| 12 | Intervention |  |  |  |  |  |  |  |  |  | **×** | **×** | **×** |  |  |
| 13 | Midline data collection |  |  |  |  |  |  |  |  |  | **×** | **×** | **×** |  |  |
| 14 | Midline data analysis |  |  |  |  |  |  |  |  |  |  |  | **×** |  |  |
| 15 | Endline data collection |  |  |  |  |  |  |  |  |  |  |  | **×** |  |  |
| 16 | Endline data analysis |  |  |  |  |  |  |  |  |  |  |  | **×** |  |  |
| 17 | Literature review |  |  |  |  |  |  |  |  |  |  |  |  | **×** |  |
| 18 | Report writing |  |  |  |  |  |  |  |  |  |  |  |  |  | **×** |
| 19 | Dissemination of report |  |  |  |  |  |  |  |  |  |  |  |  |  | **×** |

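### The work plan takes the end-line HbA1c about three months after baseline, although the methods fix the primary HbA1c at six months with monthly dietitian contact up to it

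*Protocol*

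**What the plan says.** **Time of the HbA1c.** The Project summary defines the primary outcome as the between-arm difference in mean HbA1c change to 6 months, with midline at three months and end line at six. Section 7.9 says "The study will be carried out for six months", counted from baseline to end-line collection. The Tools and procedure list says that the blood tests, HbA1c among them, "will be measured at baselines, three months and six months".

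**Dietitian contact.** The Project summary says "the diet plan will be face-to-face individual basis at the time of enrollment and follow-ups will be done every month". Section 7.11 says of the counselling phase "Every month, follow-up will be done to reemphasize the key message", and of the diet-plan phase that sessions serve the aim of "controlling the serving size of foods every month which will be lasted for 45-60 minutes", adding "Follow up will be done every month". The 45 to 60 minutes is the length of a session. No section gives a number of sessions or a month in which contact ends. For dietary intake, the Tools and procedure text places end line after the intervention: "Dietary intake assessment will be assessed before intervention (baseline) and after intervention (end line").

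**Work plan.** The Gantt chart has a row "12 | Intervention" marked in May, June and July 2021. Baseline data collection is marked in April 2021. Midline collection (row 13) is marked in May to July. Midline analysis, end-line collection and end-line analysis (rows 14 to 16) are all marked in July. Report writing and dissemination (rows 18 and 19) are marked in October. The chart has no August column.

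**Budget.** Line A4 pays one dietitian for 3 months. Line A3 pays two student enumerators for 3 months.

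**The concern.** The methods text describes monthly contact that continues until an HbA1c reading at six months. The chart describes contact and measurement that are both finished by July, after an April baseline. A team working to the chart would draw the primary HbA1c in the month when the midline sample falls due, so there would be no separate three-month and six-month values, and contact would stop there. What is at stake is when the primary outcome is read and how long the tested programme runs. A result obtained on the chart's schedule would not be the six-month result that the protocol defines. Section 7.11 would not expose the departure, because it never says how long contact lasts. The monthly monitoring checklist would show what was delivered, but only afterwards.

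**Working it through.** No sample-size or power figure bears on this point. The check sets the chart's calendar against the methods' calendar.

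**Step 1: read the chart.** The header has 14 month columns: 2 for 2019, 3 unlabelled ones for 2020, and 9 for 2021 (January to July, September, October). Each relevant row has 14 cells.

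| Activity | Marked column(s) | Month(s), 2021 |
| --- | --- | --- |
| Finalization of participants (row 11) | 8 | March |
| Baseline collection | 9 | April |
| Intervention (row 12) | 10-12 | May-July |
| Midline collection (row 13) | 10-12 | May-July |
| Midline analysis (row 14) | 12 | July |
| End-line collection (row 15) | 12 | July |
| End-line analysis (row 16) | 12 | July |
| Report and dissemination (rows 18, 19) | 14 | October |

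**Step 2: interval from baseline to end line on the chart.**
- Mid-April to mid-July: 3 months.
- Shortest, 30 April to 1 July: about 2 months.
- Longest, 1 April to 31 July: about 4 months.

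**Step 3: interval in the methods.** Six months. An April baseline gives April + 3 = July for midline and April + 6 = October for end line. July, the chart's end-line month, is therefore the methods' midline month. October, the chart's reporting month, is the methods' end-line month.

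**Step 4: can another reading of the chart reach six months?**
- Suppose the table shifted by one column when it was read from the PDF. Baseline and end line would still be three columns apart. Even if that gap spanned the absent August (May to September), the longest possible interval would be 1 May to 30 September, about 5 months.
- Suppose the clock started in March, when participants are finalised. March to July is 4 months, with a range of 3 (31 March to 1 July) to 5 (1 March to 31 July).
- Neither reaches 6.

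**Step 5: contact period.** The chart schedules 3 months (May to July). The methods imply monthly contact from enrolment to the six-month end line, about 6 months. The ratio is 3/6 = 50%. I state this in months because the protocol gives no session count. A percentage of sessions would depend on whether the enrolment session and the month-6 visit are counted.

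**Step 6: budget lines.**
- A4: 1 person × 3 months × 0.5 × 4,000 = 6,000, as printed. Six months: 1 × 6 × 0.5 × 4,000 = 12,000. Difference 6,000; with the 10% overhead, 6,000 × 1.10 = 6,600. Against the grand total: 6,000/400,000 = 1.5% and 6,600/400,000 = 1.65%.
- A3: 2 × 3 × 0.5 × 4,000 = 12,000, but 10,000 is printed. Three more months would add 10,000 to 12,000, if they are needed.
- C1 and C2 (enumerator travel and allowances): 72 days, 14,400 each. Whether the days increase is not stated.
- B1 (blood tests): 2 units are listed, although the justification names baseline, midline and end line. At the listed 600, three rounds cost 156 × 3 × 600 = 280,800, against 202,800 printed.

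**The case against.** The strongest reply is that the protocol leaves no real doubt about the primary time point. Three places in the text say six months and one administrative chart says otherwise. The chart also looks like a badly filled grant timeline. It places the literature review after the end-line analysis, runs midline collection alongside the whole intervention, and puts midline analysis and end-line collection in the same month. On this view staff would follow the methods.

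Most of that stands, and it limits the point. A reader might infer that the protocol leaves the primary time point open, or offers a rival three-month design. The Project summary, section 7.9 and the Tools and procedure text do not support that: six months is settled. (The same list also puts the PAID score at 12 months. That is a separate timing conflict and does not touch HbA1c.) A reader might also picture a team that moves only the end line to October and leaves contact ending in July, so that the primary HbA1c follows some months without contact. No part of the protocol proposes this. Monthly contact with no earlier stop, and an end line placed after the intervention, imply contact up to month 6.

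Nor does the budget show that only three months can be delivered. A4 is described as a minimum fee, section 7.11 describes the dietitian as working at the participating centre, and A3 does not multiply out to its printed total. The three funded months agree with the chart but do not prove the dose.

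What the reply does not remove is the contradiction itself. The chart is the only place in the protocol that dates the intervention and the visits, and it cannot be reconciled with six months.

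**Conclusion.** The point holds as an error in the Work plan. The chart puts end-line HbA1c about 3 months after baseline (2 to 4), where the methods require 6, and schedules 3 of about 6 implied months of contact. Followed as printed, it would read the primary outcome at the time of the three-month midline.

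This rests on the chart's columns as they appear in the text, and a one-column shift does not change the conclusion. The six-month contact period is an inference from monthly contact with no earlier stop and an end line placed after the intervention; it is not stated in words. No effect on the size of the HbA1c difference, on power or on bias is claimed, because the documents give no basis for one. The correction matters because it decides when the primary outcome is read and how long the programme runs.

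**What to change.** **Work plan.**
- Add the missing August column and extend row 12 to month 6, which is October 2021 for an April baseline.
- Put the three-month midline (row 13) in July.
- Move end-line collection and analysis (rows 15 and 16) to October or later. Enrolment is consecutive, so each participant's six-month visit follows that participant's own enrolment date.
- Move report writing and dissemination (rows 18 and 19) after that.

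**Section 7.11.** State that monthly dietitian contact runs from enrolment to month 6, and say whether the enrolment session and the month-6 contact count as sessions.

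**Budget.** Set A4 to 6 months: NRs 6,000 more, or 6,600 with overhead. Check A3, C1 and C2 for extra enumerator time. Check B1 as well: the methods already require three blood rounds, so the fix adds none, but the line lists 2 units.

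**Cost.** Reporting moves a few months later. The A4 increase is a lower bound, and the documents do not fix an upper limit. No new procedure or type of staff is needed.

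**If only three months can be delivered,** restate the programme length and the primary time point, with the objective and conclusion to match, through an amendment approved by the Nepal Health Research Council. The Ethical issues section already provides for that route.
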